## Abstract

**Background:** Both anxiety and depression in family caregivers (FCs) of advanced cancer patients are common, and they have a negative influence on both the FCs and the patients. Some studies suggested that a variety of interventions could alleviate the psychological symptoms of FCs. However, there is no consensus on much more effective methods for intervention, and relatively high-quality research is blank in psychological problems of these population in China. The validity of mindfulness-based stress reduction (MBSR) and psychological consultation guided by the needs assessment tool (NST) in the psychological status of caregivers will be compared in this study to select a more suitable intervention for the FCs of advanced cancer patients in China.

**Methods and Analysis:** A randomized N-of-1 trial would be conducted at the Cancer Hospital, Chinese Academy of Medical Sciences. Fifty eligible FCs of advanced cancer patients will be recruited, and all will receive three cycles of psychological intervention treatment, with each cycle including both of MBSR and psychological consultation guided by the NST. MBSR and psychological consultation guided by the NST will be compared with each other in each cycle, and the intervention sequence will be based on the random number table generated after the informed consent has been completed. Each treatment period is 2 weeks, and the interval between different treatment cycles or treatment periods is 1 week. The self-reported scales are measured at the beginning and end of each treatment period, including the Self-Rating Anxiety Scale (SAS), the Self-Rating Depression Scale (SDS), Distress Thermometer (DT), Zarit Burden Interview (ZBI), Chinese version of the Medical Outcomes Study 12-item Short Form (C-SF-12), and Family Carer Satisfaction with Palliative Care scale (FAMCARE-2).

**Dissemination:** The protocol of the study was approved by the Institutional Review Board of the Ethical Committee of the Cancer Hospital, Chinese Academic of Medical Science. The results will be published in a peer-reviewed medical journal. The study is registered at Chinese Clinical Trials Registry with the trial registration number chiCTR2000033707. This study employs an innovative methodological approach on the effectiveness of MBSR and psychological consultation guided by the NST for psychological status of FCs of advanced cancer patients. The findings of the study will be helpful to provide high-quality evidence-based medical data for psychological intervention of FCs of advanced cancer patients, and guide clinicians on best quality treatment recommendations.

## Introduction

Cancer has become a major health problem worldwide, with an estimated 18.1 million new cases and 9.6 million deaths in 2018 (Bray et al., 2018). In China, 3.3 million new cases and 2.4 million deaths occurred in 2015 (Zheng et al., 2019). In the past 10 years, the incidence and mortality rate of cancer in China have maintained annual growth rates of 3.9 and 2.5%, respectively (Chen et al., 2018). Much of the rising burden lead to cost and society problem besides medical problems, as well as psychosocial issues. Cancer is a severe stressful event for both patients and family caregivers (FCs), and cancer is the third most common reason for adult caregiving (Kent et al., 2016; Sun et al., 2019). FCs have to offer physical and emotional care for cancer patients, and they suffer financial, social, physical, and mental burdens (Geng et al., 2018; Wang et al., 2018; Alam et al., 2020; Duimering et al., 2020). FCs of advanced cancer patients are at greater risk for psychological problems or distress than FCs of other kinds of patients, which is likely due to the deterioration of the disease, serious adverse reactions related to anticancer treatment, and more intolerable severe symptoms at the end of life (Tang, 2006; Williams and Mccorkle, 2011; Oechsle et al., 2019; Teixeira et al., 2019; Lin et al., 2020). Psychological problems, mainly anxiety and depression, also have profound adverse effects on the quality of life QOL of both patients and caregivers (Sun et al., 2019; Teixeira et al., 2019). The prevalence rates of significant anxiety and depression among FCs of advanced cancer patients vary largely, from 40 to 47% and from 16 to 67%, respectively (Oechsle et al., 2019; Teo et al., 2019; Alam et al., 2020).

Family-centered palliative care may improve the outcomes of both FCs and patients (Kent et al., 2016; Ferrell et al., 2017). However, both research and practice evidence are mostly limited to patients, and the psychological needs and care of FCs are often neglected (Kent et al., 2016). Few studies on psychological interventions for FCs in advanced cancer patients are found in the literature, but the number is growing. Some studies documented improvements in anxiety and depression resulting from early and standard psychological interventions (Fu et al., 2017; Alam et al., 2020). Few high-level evidence-based medical studies on the effectiveness of different interventions in China have been reported, and there is no consensus or guideline on psychological intervention among FCs of advanced cancer patients (Fu et al., 2017; Geng et al., 2018).

At present, mindfulness-based stress reduction (MBSR) and psychological consultation guided by the needs assessment tool (NST) are relatively widely used among FCs of advanced cancer patients (Zhang et al., 2015; Zimmermann et al., 2018). Previous studies found that both classic 8-week MBSR sessions and abbreviated 2-week sessions were effective in reducing depression, anxiety, and distress (Grossman et al., 2004; Khoury et al., 2015; Quinones and Griffiths, 2019; Wathugala et al., 2019). MBSR helps FCs focus on the current physical and mental state, primarily through meditation, to accept the state in a positive way. The psychological consultation guided by the NST is carried out by professionals after they assess the unmet needs of FCs through scales. MBSR is a kind of group intervention, which does not aim at individual specific problems. Psychological consultation is a one-to-one form, which requires more manpower and time. So far, there are no clinical trials directly comparing these two interventional techniques among FCs. Most previous studies are conventional prospective randomized controlled studies comparing the differences between the groups, but personalized intervention and assessment are the keys to explain the effectiveness of psychological intervention.

N-of-1 trials, which are within-patient randomized multi-period crossover trials that compare two different therapeutic strategies, provide the highest level evidence of intervention effects for individuals, and enhance precision when intervention effects are heterogeneous between individuals (Mirza and Guyatt, 2018; Porcino et al., 2020). At least 2 cycles with 4 periods are needed to compare the effectiveness and give much more accurate. In our study, because of the high quality of compliance, 3 cycles with 6 periods are designed and are available.

Therefore, we plan to conduct this study through an N-of-1 trial, in which the bias resulting from the difference between individuals can be minimized to the greatest extent. In the protocol, the design of this N-of-1 trials is given in detail. The main purpose of the study is to compare the effect of MBSR and psychological consultation guided by the NST on the psychological well-being and QOL of FCs of advanced cancer patients.

## Methods

### Study Design

This study is a single-case randomized controlled trial that will be conducted at the Cancer Hospital, Chinese Academy of Medical Sciences. Each FC of advanced cancer patients will receive three cycles of psychological intervention treatment, with each cycle including both of MBSR and psychological consultation guided by the NST. MBSR and psychological consultation guided by the NST will be compared with each other in each cycle, and the intervention sequence will be based on the random number table generated after the informed consent has been completed. Each treatment period is 2 weeks, and the interval between different treatment cycles or treatment periods is 1 week. The outcomes will be measured at the beginning and end of each treatment period (see Figure 1).

**Figure 1 F1:**
[figure not shown]
The flowchart of the study process.

### Sample Size Calculation

The sample size was calculated based on the previous research of Senn, and according to the power of 80% (Senn, 2002, 2019). The assumption of a minimally important difference of 0.4 SDs on the SAS and SDS interference scale (Liu and Yang, 2019). Assuming a 5% dropout rate, using a 2-group *t*-test with 2-sided alpha equalling 0.05, 300 periods (50 participants and 6 periods for each person) would achieve study objectives.

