### Statistical Methods

For each cycle, each washout periods, and each person, the data from the baseline will be managed to conduct analysis. Outcomes will be analyzed with longitudinal mixed effects models combining baseline and each period's measurements using time, treatment, and a time-by-treatment interaction as fixed effects, and clinician and patient as random effects. A Bayesian multi-level random effects model on the outcome will be used to combine in incorporating serial correlation and other covariates for each participant by WinBUGS software (Spiegelhalter et al., 2003).

Traditional statistical method also will be used. The interactions between the intervention and covariates including age, sex, marital status, education, employment status, etc. will conduct exploratory analyses. The paired *t*-test will be used to compare the continuous quantitative data between the two groups, and the paired chi-squared test will be used to classify the data. The measurement data will be expressed as X ± s. A *P* < *0.05* will be considered statistically significant.

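### The stated inputs give about 211 periods, not 300, and the t-test they name does not give the power of the planned within-person analysis

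*Protocol article*

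**What the plan says.** Sample Size Calculation gives a full set of inputs. It aims at 80% power and assumes "a minimally important difference of 0.4 SDs on the SAS and SDS interference scale". The test is a two-group t-test "with 2-sided alpha equalling 0.05". Loss is set by "Assuming a 5% dropout rate". The result is that "300 periods (50 participants and 6 periods for each person) would achieve study objectives". The method is credited to cited methodological work, but no formula, within-person SD or between-person variation in treatment effect is given.

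Elsewhere the trial is within-person. Under Study Design, each caregiver goes through three cycles and each cycle contains both interventions, so every participant contributes three periods of each. Statistical Methods says "Outcomes will be analyzed with longitudinal mixed effects models combining baseline and each period's measurements", with patient and clinician as random effects, and adds a paired t-test. Primary Outcome describes the SAS and SDS only as 20-item self-report questionnaires.

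**The concern.** The article states inputs, a test and a result, so the result can be checked, and it does not follow from the inputs. There are three separate faults.

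- The named formula needs far fewer periods than 300 for the power claimed.
- The named formula is not the power formula for any analysis in Statistical Methods, because it treats 300 measurements on 50 people as 300 independent observations.
- The article does not say whose SD the 0.4 refers to (between persons, within persons, or of the within-person difference), and it attaches the 0.4 to an interference scale that appears nowhere in the outcomes.

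This paragraph is the article's only quantitative justification of the trial's size. A reader or the data monitoring team would take from it 80% power for 0.4 SD, and that statement cannot be traced to the planned analysis.

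**Working it through.** **Inputs (Sample Size Calculation):** standardised difference d = 0.4; two-sided alpha 0.05; power 0.80; dropout 5%; two-group t-test. The 1:1 split of periods follows from Study Design.

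**1. The plan's own figure**

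- Normal approximation: n per treatment = 2 × ((1.960 + 0.842)/0.4)² = 98.1, so 99.
- Exact noncentral t: 99.1, so 100 per treatment and 200 in total.
- With dropout: 200/0.95 = 210.5, so 211 periods; 211/6 = 35.2, so 36 participants.
- Stated: 300 periods, 50 participants. 300/211 = 1.42, so the stated figure is 42% larger.

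**2. The same test at the stated size**

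| Periods | Power at 0.4 SD | Difference detectable at 80% power |
|---|---|---|
| 300 (150 + 150) | 93.2% | 0.32 SD |
| 285 (300 × 0.95) | 92.0% | 0.33 SD |

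**3. Variants that might explain 300** (periods after 5% dropout)

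| Variant | Periods |
|---|---|
| One-sided alpha 0.05 | 165 |
| Alpha 0.025 for two scales | 255 |
| 80% power on both scales, taken as independent | about 274 |
| 90% power | 280 |

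None of these comes within 3% of 300. If 0.4 is instead read as a fraction of the SD of the within-person difference and a paired t-test on participants is used, 52 participants are needed, or 55 with dropout. On that reading 50 pairs give 79.2% power and 47 give 76.6%.

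**4. Power for the within-person contrast**

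With N completers and three periods of each intervention per person, the mean treatment difference has

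SE² = τ²/N + 2σ_w²/(3N),

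where σ_w² is the within-person variance of a period's measurement and τ is the SD of individual treatment effects. The documents give neither, so the values below are assumptions: total SD 1, so that σ_w² = 1 − ρ with ρ the within-person correlation; N = 47 (50 × 0.95 = 47.5, rounded down); participant-level paired t-test, two-sided alpha 0.05, difference 0.4.

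| ρ | τ | τ² + 2(1 − ρ)/3 | SE | Power |
|---|---|---|---|---|
| 0 | 0 | 0.667 | 0.119 | 91% |
| 0 | 0.4 | 0.827 | 0.133 | 84% |
| 0 | 0.6 | 1.027 | 0.148 | 75% |
| 0.5 | 0.4 | 0.493 | 0.102 | 97% |

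For the third row, SE = √(1.027/47) = 0.148 and 0.4/0.148 = 2.71 is the noncentrality on 46 degrees of freedom, giving 75%. The answer depends on τ and ρ, which the paragraph does not mention. The Introduction itself supports the N-of-1 design by its value when effects differ between individuals, so τ = 0 is not a natural default.

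**The case against.** The best defence is that the error is on the safe side. The article says that 300 periods suffice, not that 300 is the minimum or that power is exactly 80%. Under its own formula the target is exceeded. That stands, and it rules out one inference a reader might draw, namely that the trial has been shown to be underpowered. Nothing in the document shows that.

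A second defence is that 50 may come from a sound calculation badly described. With within-person SD 1, three cycles and τ² of about 0.3, the normal approximation gives (0.3 + 0.667) × (2.802/0.4)² = 47.4, so 48 participants, and 48/0.95 = 50.5, so 51. This is close to 50, and the article is condensed and cites methodological work. It is a reason to call the figure untraceable rather than to call 50 participants a wrong number. It does not rescue the text, which names a two-group t-test and gives no such variance.

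The opposite inference is also tempting: that 92% is the real power, so the trial has room for a multiplicity correction, a carryover term or heavier attrition, or could stop at 211 periods. The documents do not support this either. The 92% rests on treating repeated periods as independent. In the within-person model with ρ = 0 and τ = 0.4, testing at alpha 0.025 for two scales lowers power from 84% to 75.5%. With 40 completers at alpha 0.05 it is 77%. Any surplus depends on variances that nobody has stated.

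**Conclusion.** The point holds in a limited form. The stated inputs give 200 evaluable periods, or 211 with dropout, against 300 stated, and 300 periods correspond to about 92–93% power by the named test rather than 80%. This part needs no assumption beyond the article's own inputs.

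The named test fits neither the within-person design nor the mixed-model and paired analyses, so the power of the planned analysis is unknown. The span of about 75% to 97% rests on the assumed variances, on completers supplying all six periods, and on reading 0.4 against a total SD of 1. It shows that power could lie on either side of 80%, not where it lies. The reference to an interference scale is a wording slip, but the undefined SD is a substantive gap.

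The paragraph should be corrected. The enrolment target is not shown to be wrong.

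**What to change.** Keep 50 participants and rewrite the Sample Size Calculation paragraph:

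- replace the two-group t-test with power for the within-person contrast, SE² = τ²/N + 2σ_w²/(3N), at N = 47 completers;
- define the SD to which 0.4 refers;
- state the assumed within-person and participant-by-treatment variances with their source, and report power over a range of both;
- delete the reference to an interference scale and name the SAS and SDS scores themselves.

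Do not print 92% from the independence formula as the trial's power, do not reduce enrolment to 211 periods, and do not claim spare power for other corrections. The cost is one paragraph and a short calculation; enrolment and conduct do not change.

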### Participants Recruitment

In-patient broadcasting, flyers and science popularization presentations will be used to raise the public awareness of the study. Once the FC shows some interest of the study, informed consent and detailed explanation to recruit into the study will be given.

### Interventions

MBSR was developed by Kabat-Zinn at the University of Massachusetts Medical Center in 1979, and it has a standardized operating procedure (Zimmermann et al., 2018). In MBSR practice, individuals are encouraged to pay attention to what is happening in the moment, in a non-judgemental way, without relying on previously formed schemas. The objective of this approach is to help individuals change the way they think through mindfulness meditation and exercises. The abbreviated 2-week MBSR mainly includes Body Scan Mediation and Sitting Mediation used audio recordings from an online version of the Kabat-Zinn course (made by a certified MBSR instructor) and previous studies (Quinones and Griffiths, 2019; Wathugala et al., 2019; Potter, 2020). On the first day (the start of week 1), the participant will be taught what MBSR and Body Scan Mediation are by an expert, and all participants will practice daily while being individually guided by the special audio during days 2–14. For days 2–7, they will practice a 5-min Body Scan Mediation each day. On day 8 (the start of week 2), the participant will learn what Sitting Mediation is, and they will practice a daily 5-min Sitting Meditation during days 9–14. Meanwhile, each participant will receive an audio document and an operating manual that summarizes key points of the six sessions and clarifies homework requirements. The participants should complete the practice according the guidance of the daily audio document and record on the manual faithfully.

The psychological consultation refers to the one-to-one consultation after the analysis according to the Chinese version of the Comprehensive Needs Assessment Tool in cancer for Caregivers (CNAT-C) (Zhang et al., 2015). The CNAT-C was developed in 2011, including seven dimensions and a total of 41 items, and it has been verified to have good reliability and validity among caregivers of cancer patients in China. It was reported by Zhang that the total Cronbach's α coefficient was 0.94 and the dimensional Cronbach's α coefficient was 0.61–0.93. Consultation focusing on problems found or raised through the CNAT-C, is generally once a week, approximately 50 min each session. The specific frequency and time arrangement depend on the specific situation of the participant, and every counseling session will be recorded.

Both interventions have manuals and will be delivered by clinicians trained in the intervention for which they are responsible. All the trainers have corresponding qualification certificate and operation experience. The principle investigator of the research/ authorized clinical research coordinator will review the record of each intervention, and give back to the trainers.

### Randomization and Allocation

Random grouping will be performed by a third party who is not directly involved in the trial according to the random number table method. Computer-generated random numbers will be made and secured by the Information Technology team with SAS 9.4 software. The random number will be kept in an envelope.

### Blinding

The assessment staff and data analysts will be blind to the participants' sequence allocations. The allocation sequence would be concealed until interventions are assigned.

### Patient Safety and Quality Control

The participants will be free to change their mind about participation at any time and will be advised to see their individual doctors to discuss future routine care. The researchers can withdraw a participant at any time if serious psychological problems occur or if the participant presents with any reason to stop the psychological intervention. Termination criteria are as follows: (1) the participant complete the intervention and follow-up; (2) the end date of the study is December 31, 2021; (3) terminate the trial at the request of the ethics committee or national government department. Adherence to trial treatment will be assessed by (1) self-reporting scales by FCs of advanced cancer patients, including SAS, SDS, DT, and so on, as part of outcome data collection and (2) the record of the psychological interventions.

### Outcomes

#### Primary Outcome

The primary outcome is the psychological status, assessed by the degree of anxiety and depression measured at the beginning and end of each treatment period. The degree of anxiety and depression will be measured by the SAS and SDS, and both of them are self-report questionnaires with 20 items rated on a four-point scale (Zung, 1965, 1971).

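### Two primary scales share one unsplit 5% level, with no deciding analysis and no either-or-both rule; if either scale suffices, the two scales alone give a familywise error of about 7–10%

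*Protocol article*

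**What the plan says.** Primary Outcome defines one construct: "The primary outcome is the psychological status, assessed by the degree of anxiety and depression measured at the beginning and end of each treatment period". It then assigns two instruments: "The degree of anxiety and depression will be measured by the SAS and SDS". No composite score, order of testing or success rule joins them.

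Sample Size Calculation uses one effect for both, a "minimally important difference of 0.4 SDs on the SAS and SDS interference scale", with "2-sided alpha equalling 0.05", 80% power and 5% dropout, and arrives at 300 periods (50 participants, 6 periods each). The level is not divided between the scales.

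Statistical Methods gives three analyses. The first is a longitudinal mixed model with time, treatment and their interaction as fixed effects. The second is a Bayesian multi-level model. The section then says "Traditional statistical method also will be used", which includes a paired t-test between the two interventions. It closes with one threshold for everything: "A *P* < *0.05* will be considered statistically significant". No analysis is named as the one that decides.

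**The concern.** The abstract says that the comparison is meant to select the more suitable intervention for these caregivers, so a false positive would become a recommendation. Two primary scores, each judged at 0.05, offer two chances of one. The mixed model and the paired t-test can each produce a P value on each score, and the mixed model has two terms (treatment, and time by treatment) that could be read as the answer. The Bayesian result may disagree with both. As written, the plan does not say which result counts. This is more than missing detail: the article itself fixes the level, the threshold and the list of analyses, and together they do not hold 5% if one scale can carry the claim.

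**Working it through.** **Inputs from the article.** Two primary scales; two-sided alpha 0.05, unsplit; effect 0.4 SD; power 80%; dropout 5%; 300 periods, so 150 per intervention, or 285 (142.5 per intervention) after 5% loss.

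**Inputs assumed.** The correlation r between the SAS and SDS test statistics is not in the article; I take 0 to 0.9. The correlation between the mixed-model and t-test statistics is not given either; I take 0.8 to 0.99.

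**1. The article's own figure.** The two-group formula is n per group = 2(1.960 + 0.842)² / 0.4² = 98.1, so 99. The total is 198, and 198 / 0.95 = 208.4, so 209 periods (211 with the t distribution). The stated 300 is not reproduced. With 300 periods the formula gives about 93% power, and with 285 about 92%. This gap is a separate point, but it is why a stricter level looks affordable in step 5.

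**2. Either scale suffices, one test per scale.** Familywise error = 1 − P(|Z1| ≤ 1.96 and |Z2| ≤ 1.96), with Z1 and Z2 bivariate normal. At r = 0 this is 1 − 0.95² = 9.75%.

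| r (assumed) | 0.05 per scale | 0.025 per scale |
|---|---|---|
| 0 | 9.75% | 4.9% |
| 0.5 | 9.1% | 4.6% |
| 0.7 | 8.35% | 4.3% |
| 0.8 | 7.8% | 4.0% |
| 0.9 | 7.0% | 3.6% |

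**3. Both scales required.** If neither scale has an effect, P(both significant) = 0.05 + 0.05 − the familywise error above: 0.25% at r = 0, 0.9% at 0.5, 1.7% at 0.7, 2.2% at 0.8. If one scale has a real effect and the other none, a claim on both still needs the null scale to reach 0.05, so the error cannot exceed 5%. Under this rule an unsplit 0.05 is correct.

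**4. Choosing between methods.** The Bayesian model gives a posterior, not a P value, so at most two methods per scale meet the threshold. If any of the four P values counted, simulation gives 8.8% to 14.0% (r from 0.5 to 0.8, between-method correlation from 0.99 down to 0.8). This is illustrative, because neither correlation is known.

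**5. Power at the stricter level.** Two-group t-test, 0.4 SD, alpha 0.025: 88.6% with 300 periods and 86.9% with 285. At 80% power, n per group = 2(2.241 + 0.842)² / 0.4² = 118.8, so 119. The total is 238, and 238 / 0.95 = 250.5, so 251 periods. These figures treat all periods as independent, as the article's formula does, although they come from 50 people with 6 periods each.

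**6. Power if both are required.** From about 92% per scale at 285 periods, joint power is at least 1 − 2 × 0.08 = 84% whatever the correlation, under the same formula.

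**The case against.** A reader might infer that the trial's false-positive rate simply is 8–10%, or nearly double the stated rate. The article does not support that. It never says that a win on either scale, by any method, is enough. The sentence ending "will be considered statistically significant" labels a test result; it does not define when one intervention is declared better. The outcome is worded as one construct covering anxiety and depression, which fits a both-scales rule too, and then the error does not exceed 5%. No familywise rate is stated that could be doubled. Nor does a two-scale, one-test figure include the effect of several methods, and it falls below 8% at r = 0.8. All of this stands, and the size must be conditional.

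It can also be said that multiplicity rules and the choice of primary analysis often sit in an analysis plan that is not shown, that the mixed model comes first in the text, that covariate interactions are already exploratory and that the other scales are already called secondary. Part of this stands: another document may settle the rule. But the article sets the level and the competing analyses itself, and order of mention is not a ranking.

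Two features also sit poorly with a tacit both-scales rule. Inclusion requires a score above 50 on only one of the two scales, and the sample size makes no allowance for joint power: at 80% per scale, joint power would be 64% at r = 0 and about 71% at r = 0.7. These are hints, not proof.

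**Conclusion.** The point holds in conditional form. Two primary scales, one unsplit two-sided 0.05, a flat threshold and no deciding analysis are all in the text; the success rule is not. If significance on either scale suffices, the two scales with one test each carry a familywise error of about 7–10% for assumed correlations from 0.9 down to 0. Choosing between the mixed model and the paired t-test can only add to that, by an amount the article does not allow one to fix. If both scales are required, the error is at or below 5% and the level needs no split. Either way the rule and the deciding contrast have to be written down before the data are seen.

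**What to change.** 1. Name one mixed-model contrast as the deciding analysis for each scale: MBSR versus consultation at the end of the period, stating how the treatment and time-by-treatment terms define it.
2. Choose one success rule. Either test SAS and SDS with Holm at an overall 0.05 (smaller P against 0.025; if that succeeds, the larger against 0.05), or state that both must reach 0.05.
3. Label the paired t-test and the Bayesian model supportive, and make no confirmatory claims from the secondary scales.

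**Cost.** A few sentences. Under the article's own two-group formula at 285 periods, power per scale falls from about 92% to about 87% at Holm's 0.025 step, still above the stated 80%. Under the both-scales rule, joint power is at least 84%. Both figures rest on treating periods as independent. Power under the mixed model depends on within-person variance and correlation that the article does not give, so it should be checked before claiming that no further participants are needed.
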